### Concealment mechanism {16b}

Numbers according to treatments will be kept in opaque envelopes:Number 1 – Traditional caries removal with a low-speed drill (Group 1);Number 2 – Partial removal of carious tissue with the administration of Papacarie™ (Group 2);Number 3 – Partial removal of carious tissue with the administration of Papacarie™ and application of *Bixa orellana* extract (20%) (Group 3); andNumber 4 – Partial removal of carious tissue with the administration of Papacarie™, application of *Bixa orellana* extract (20%), and LED (aPDT) (Group 4).

### Implementation {16c}

The researchers responsible for the treatment application will enroll participants and assign participants to interventions, only the outcome assessors will be blind. The allocation sequence will be made by a different researcher, who will not be involved in the procedures.

## Assignment of interventions: blinding

### Who will be blinded {17a}

The clinical evaluations of the carious tissue removal, as well as the microbiological and radiographic analyses, will be performed by examiners blinded to the treatments performed on each tooth. Only the researcher in charge of procedures will know to which group the participants belong.

### Procedure for unblinding if needed {17b}

As the researchers responsible for clinical care are aware of the participant allocation, unblinding of the assessors would not be required.

## Data collection and management

### Plans for assessment and collection of outcomes {18a}

Researchers will be previously trained to collect data and perform evaluations, according to the parameters described in outcome measures. The previously trained examiner will evaluate all cavities after the respective interventions and will test the hardness of the remaining dentin. For carious tissue to be considered removed, there must be an agreement between the operator and the examiner. To determine interexaminer agreement regarding the clinical and radiographic evaluations by examiners, the calculation of Kappa coefficients will be used at baseline and follow-up appointments. Interexaminer agreement must be greater than 85% (*K*>0.85) Firstly, the researchers responsible for the procedures will write the information in paper case report forms. Then, the data will be entered electronically in Excel datasets, in computers to which only the authors will have access.

### Plans to promote participant retention and complete follow-up {18b}

As participants will already be in pediatric dentistry treatment, we believe recruitment will be feasible. We believe participants will be present for the follow-ups due to concerns and other possible treatments in the clinic. Phone texts and calls will also be used as visit reminders.

### Data management {19}

All data will be entered electronically, in Excel files, and stored in computers and hard discs. The participants’ files will be accessible only to the authors of this study and only they will be able to edit the information, maintaining data accuracy and validation.

### Confidentiality {27}

The data sets generated and analyzed during the study will be available from the corresponding author at reasonable request. Once the data is entered electronically, participants’ identification details will no longer be attached to their data, they will be reported only by codes. After the analysis of the data, volunteers will be invited to a meeting and the results will be shared, in case they wish to attend it. The authors also intend to publish the results.

### Plans for collection, laboratory evaluation, and storage of biological specimens for genetic or molecular analysis in this trial/future use {33}

Not applicable.

## Statistical methods

### Statistical methods for primary and secondary outcomes {20a}

The data will be stored in Excel datasets and analyzed statistically by employing different tests and considering a 5% level of significance. Only the researchers involved in the study will have access to the data, even if the study is discontinued. The results will be submitted to the Shapiro-Wilk test to check for normality. In case data distribution is normal, analysis of variance (ANOVA) will be used for both the dependent and independent variables. In case the data distribution is not normal, the Friedman test will be used for the dependent variables, followed by the Wilcoxon test as post hoc. For independent variables, the Kruskal-Wallis test will be used, followed by the Mann-Whitney test as post hoc. Pearson (for normal data) or Spearman (for non-parametric data) correlation coefficients may be calculated to determine correlations among the variables.

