**Methods:**

A total of 160 teeth with deep occlusal dental caries will be selected and divided into 4 groups: G1 - control group (Caries removal with a low-speed drill); G2 - Partial Caries Removal with Papacarie™ (Fórmula e Ação, São Paulo, SP, Brazil); G3 - Partial Caries Removal with Papacarie™ and application *Bixa orellana* extract (20%) (Fórmula e Ação, São Paulo, SP, Brazil); G4 - Partial Caries Removal with Papacarie™ and application *Bixa orellana* extract (20%) with LED (Valo Cordless Ultradent®, South Jordan, UT, USA) (aPDT). After treatment, all the teeth will be restored with glass ionomer cement and followed up clinically and radiographically, with evaluations at immediately, 1 week, and 1, 3, 6, and 12 months. Dentin samples before and after treatment will be analyzed microbiologically. The efficacy of treatments will be assessed with microbiological (colony-forming units, before and after carious tissue removal), radiographic (integrity of the periapical area and eventual changes in the radiolucent zones), and clinical examinations (retention of the restorative material in the cavity and occurrence of secondary caries), as well as with the time required for the procedures and the need for anesthesia during the procedures. In case data distribution is normal, analysis of variance (ANOVA) will be used for both the dependent and independent variables. In case the data distribution is not normal, the Friedman test will be used for the dependent variables. For independent variables, the Kruskal-Wallis test will be used.

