Aliquots (100 ml) from each dilution will be sewn onto the surface of agar and spread with the aid of a Drigalski spatula. Undiluted aliquots and aliquots from dilution 10^2^ (100 ml) will be pour-plated on Rogosa SL agar (Difco Laboratories, Detroit, Michigan) for the determination of lactobacilli (LB). The Brucella agar dishes will be incubated in an anaerobic chamber (PLAS by LABS, Lansing, MI) at 37°C for 7 days. The Mitis Salivarius agar and Mitis Salivarius Bacitracin dishes will be incubated in a 10% CO_2_ atmosphere (CO_2_ greenhouse, Shel Lab, mod. 2123, Oregon) at 37°C for 48 h. The dishes containing Rogosa agar will be incubated in a 10% CO_2_ atmosphere at 37°C for 72 h. After incubation, the characteristic colonies in each dish will be counted with the aid of a stereomicroscope at a magnification of 10 times in dilutions with 30 to 300 colonies per dish. All procedures will be performed in duplicate, and the mean of the counts will be calculated. The results will be expressed in colony-forming units (CFU) of SM and LB as well as in proportion of streptococcus (% S/VM), SM group (% SM/VM and lactobacilli (% LB/VM) in relation to the total of viable microorganisms (VM). For SM, the proportion in relation to the total of streptococci (% SM/S) will also be calculated. Immediately after the removal of the carious tissue, samples of the remaining dentin will be taken with a Meyhoefer auricular n° 2 curette and the procedures will be repeated [14].

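### A Shapiro-Wilk result on the trial's own data chooses between ANOVA and rank tests, so the primary microbiological and radiographic tests are not fixed in advance

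*Protocol article*

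**What the plan says.** The statistical methods section {20a} says the data will be "analyzed statistically by employing different tests and considering a 5% level of significance". It continues: "The results will be submitted to the Shapiro-Wilk test to check for normality". Two branches follow.

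- Normal: "In case data distribution is normal, analysis of variance (ANOVA) will be used for both the dependent and independent variables".
- Not normal: Friedman with Wilcoxon post hoc for the dependent (repeated) variables. Between groups, "For independent variables, the Kruskal-Wallis test will be used, followed by the Mann-Whitney test as post hoc".

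The abstract repeats the branches: "In case the data distribution is not normal, the Friedman test will be used for the dependent variables". Neither place says what is tested for normality (pooled values, arms, arm-and-visit cells or residuals), or how several normality results for one outcome are combined.

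Outcomes {12} makes the microbiological, radiographic and clinical evaluations all primary. For the first, "The results will be expressed in colony-forming units (CFU) of SM and LB", together with percentages of viable organisms; no transformation is named. Each tooth gives a sample before removal and another after it: "Immediately after the removal of the carious tissue, samples of the remaining dentin will be taken". Radiographic density change is obtained by digital subtraction at six named times, from immediately after treatment to 12 months.

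**The concern.** A preliminary significance test on the outcome values settles how the treatment question is answered. ANOVA compares means; Kruskal-Wallis and Friedman compare ranks. Which applies is unknown until the data are in, may differ from one primary outcome to the next, and depends on a result unrelated to treatment. Because the unit tested is not stated, an analyst must also choose it once data exist, and that choice can change the branch.

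For CFU there is a second problem. The design is before and after in four parallel arms, so the natural question is whether the reduction differs by arm. In the rank branch Friedman compares times within subjects, and Kruskal-Wallis compares arms without using the baseline sample. Neither, as written, answers that question.

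**Working it through.** **Inputs from the protocol.** 4 arms and 160 teeth (abstract); at least 34 per group, 40 recruited (Sample size {14}); 5% level ({20a}); two CFU samples per tooth; six radiographic times. The assumptions behind the 34 are in figures not shown, so it cannot be reproduced from the readable text. This point uses 34 only as the number per arm.

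**Assumed, because the protocol does not say.** Shapiro-Wilk at 5%; one rejection moves the whole outcome to ranks; CFU log-normal, with the spread shown as a range.

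**1. Switching by chance on normal data.** One test rejects about 5% of the time (simulated 4.9% at n = 34). For k independent tests, P(at least one rejection) = 1 - 0.95^k.

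| Unit tested | k | Probability |
|---|---|---|
| Arms at one time | 4 | 0.185 |
| Arms x 2 CFU samples | 8 | 0.337 |
| Arms x 5 radiographic visits | 20 | 0.642 |
| Arms x 6 radiographic visits | 24 | 0.708 |

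The count is 20 or 24 because the Radiographic evaluation section refers in one place to the initial exams and in another to the image taken immediately after treatment as the reference. If the latter, the immediate visit has no change to test. With correlated visits, simulation at k = 24 gave 0.715 (correlation 0.5) and 0.631 (correlation 0.8).

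**2. Where untransformed CFU would go.** Simulated rejection rate for log-normal counts at n = 34: about 0.87 at log10 SD 0.25 (0.86-0.87 across runs), 0.999 or more at 0.5, and 1.00 at 1.0. At smaller spreads it falls: 0.73 at 0.2 and 0.25 at 0.1.

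**3. What the rank branch then tests.** With two times, Friedman is a sign test of before against after. Suppose it is run within each arm and every arm has the same true 0.5 log10 reduction (log10 SD 1, correlation 0.5, n = 34). Each arm is significant with probability 0.6545. The chance that some arms are significant and others not is 1 - 0.6545^4 - 0.3455^4 = 1 - 0.1835 - 0.0142 = 0.80, with no difference between arms.

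**4. Type I error of the between-arm test.** Simulating the two-step rule on post-treatment values (4 arms, n = 34, any arm rejecting leads to Kruskal-Wallis) gave 0.058 on normal data and 0.043 on log-normal data. The simulation error is about sqrt(0.05 x 0.95 / 2000) = 0.005, so neither departs materially from 5%.

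**5. Power.** Assumed: log10 SD 1, before/after correlation 0.5, one arm 0.6 log10 lower, n = 34.

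| Analysis of post-treatment CFU | Power |
|---|---|
| Two-step rule (always Kruskal-Wallis here) | about 0.68 |
| ANOVA on log10, no baseline | 0.71 |
| ANCOVA on log10 with log10 baseline | about 0.84 (0.83-0.84 across runs) |
| ANOVA on raw CFU | 0.06 |

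Most of the gain comes from the baseline term (0.71 to 0.84), little from leaving ranks (0.68 to 0.71).

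**The case against.** The rule is announced in advance, and a reader who infers from it an inflated false-positive rate would be wrong: step 4 shows none of note. For skewed raw counts it also steers away from the worse test (0.68 against 0.06), and Kruskal-Wallis on post-treatment values remains a valid randomised comparison. All of this stands.

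A reader might also infer that a chance rejection leaves no way to compare radiographic change between arms. The protocol does not support that. Density is itself a subtraction value, so Kruskal-Wallis at a visit compares change between arms; only a joint analysis across visits is lacking. Nor should 71% be read as the protocol's own switching rate: it requires per-cell testing and a one-rejection rule, neither stated.

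Analysis of CFU on the raw scale is likewise an inference. The microbiological section gives the units of reporting and does not exclude a log transformation, which a separate analysis plan could name. If the spread is wide, untransformed CFU would not flip at random either; it would go to ranks nearly every time.

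Finally, the ANOVA branch names no arm-by-time term, so deleting the normality test alone would not supply one.

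What survives is the explicit switch. It is a stated rule rather than a detail left for later, and an analysis plan could remove it only by contradicting the published text.

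**Conclusion.** The point holds in a limited form. Section {20a} leaves the primary test and estimand for the microbiological and radiographic outcomes to a normality test on the outcome data. Chance switching on normal data is 5% per test, about 19% over 4 arms and 64-71% over 20-24 independent cells, under the unstated testing rule assumed above. If CFU is untransformed and log-normal with log10 SD of at least 0.25, it reaches the rank branch about 86-100% of the time, where the before-to-after change is not compared between arms as written. The power loss, about 0.68 against 0.84, belongs to one assumed scenario and comes mainly from ignoring the baseline. Validity of the between-arm test is not in doubt. This should be corrected before analysis.

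**What to change.** In {20a}, delete the Shapiro-Wilk switch and name one primary method per outcome.

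- **CFU:** log10 post-treatment count in a linear model with arm and log10 baseline count (ANCOVA), with a stated rule for zero or uncountable plates. The rule matters because only dishes with 30 to 300 colonies are counted.
- **Radiolucent-zone density change:** linear mixed model with arm, visit and arm-by-visit, reporting 12-month arm differences with 95% confidence intervals. State which image is the reference.
- **Procedure time:** linear model on log time.
- **Face scale and 0-9 clinical score:** a method suited to ordinal or categorical data.

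Use residual plots as diagnostics and rank tests as a stated sensitivity analysis that does not replace the main result. Make the abstract agree.

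The cost is one rewritten paragraph, slightly more modelling work and a convention for zero counts. No clinical procedure or data collection changes.

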### Eligibility criteria {10}

#### Inclusion criteria

Adequate health with no systemic conditions (ASA 1);Adequate cooperation (scores 1 or 2 in Wright’s modification of Frankl’s behavior scale);Clinically presenting at least 1 permanent molar with an acute, active caries on the dentin not surpassing 2/3 and only involving the occlusal face, with direct view and access as well as no clinical or radiographic signs of pulp involvement. It is not intended to include more than one tooth per participant;Six to 12 years of age;Scores 3 (localized enamel breakdown due to caries with no visible dentine), 4 (underlying dark shadow from dentine), or 5 (distinct cavity with visible dentine) of the International Caries Detection and Assessment System criteria (ICDAS), in the occlusal surface; andThe setting to access these criteria will be during a clinical and radiographic examination, performed in the pediatric clinic of the dentistry course of Paulo Picanço School of Dentistry.

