#### Microbiological evaluation

This is one of the primary outcomes of the study. A sample of caries-affected dentin will be taken from each selected tooth before the removal of the carious tissue. The samples will be standardized with the use of a Meyhoefer auricular curette n° 2 (ABC Instrumentos Cirúrgicos, São Paulo, Brazil), because it has a hole in its tip, and placed into test tubes containing 3.8 ml of the transport medium (Phosphate Buffered Saline (PBS) - Thermo Fisher Scientific, Massachusetts, EUA). The dental tissue will be dispersed in the transport tube (Microtubo Tipo Eppendorf Cap. 1.5 ml – GlobalPastic, São Paulo, Brazil) containing glass pearls through agitation at maximum speed in a vortex device (Agitador Para Tubos Vortex – Kasvi, Paraná, Brazil) for 30 s to homogenize the biological material. The biofilm will be diluted in series on the order of 10^1^ to 10^6^ in peptone water and inoculated in culture media in Petri dishes (Placa de Petri Descartável Estéril - PRO-LAB MATERIAIS PARA LABORATORIOS LTDA, São Paulo, Brazil). Aliquots of dilutions 10^4^, 10^5^, and 10^6^ will be sewn on the surface of Brucella agar (Difco Laboratories, Detroit, Michigan) containing defibrinated sheep blood (50ml/L), hemin (5 mg/ml), and menadione (10mg/ml) for the determination of the total number of viable microorganisms (VM). Aliquots of dilutions 10^3^ and 10^4^ will be sewn on Mitis Salivarius agar (Difco Laboratories, Detroit, Michigan) for the determination of the total number of streptococcus (S). Aliquots of dilutions 10^1^ and 10^2^ will be sewn on Mitis Salivarius agar with the addition of debacitracin for the determination of the population of streptococcus of the mutans group (SM).

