### Sample size {14}

The sample size was calculated based on a previous study in the literature [16, 17] (Fig. 2), considering the expected difference and standard deviation and weighting colony-forming units (CFU) of bacteria. For the statistical calculation, paired samples were considered, with α=5% and an 80% test power. The minimum number in this clinical trial was determined to be 34 teeth per group. Therefore, 40 teeth per group will be recruited to compensate for possible dropouts during the experimental period. G*Power 3.1 was used to perform the calculations (Fig. 3).

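### The named between-arm tests for CFU carry no adjustment for the pre-treatment count taken from every tooth; baseline-adjusted analysis would be more precise at almost no cost

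*Protocol article*

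**What the plan says.** Under Microbiological evaluation, the protocol article states: "A sample of caries-affected dentin will be taken from each selected tooth before the removal of the carious tissue". A second sample follows immediately after removal and goes through the same laboratory steps, so each tooth has a before and an after count on the same media. Outcomes {12} makes the microbiological evaluation a primary outcome, and Sample size {14} rests on CFU.

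Statistical methods {20a} chooses the test by a normality check: "The results will be submitted to the Shapiro-Wilk test to check for normality". Normal data go to ANOVA, without saying whether one-way, repeated-measures or mixed. Non-normal data go to Friedman and Wilcoxon for what the text calls dependent variables. Between arms the text reads: "For independent variables, the Kruskal-Wallis test will be used, followed by the Mann-Whitney test as post hoc". No covariate is named in any branch.

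No section says which CFU quantity enters the between-arm test. Microbiological evaluation lists counts and proportions and defines neither a change nor a log reduction.

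**The concern.** The section on the choice of comparators asks which of the four treatments is more efficient. With one tooth per child, that is a comparison of independent arms. The pre-treatment count is the obvious covariate for it and is already being collected. Kruskal-Wallis and Mann-Whitney take no covariate, and Friedman and Wilcoxon, which do use the pairing, compare time points rather than arms. Under the named tests the baseline can reach the arm comparison only through a change score or through a group-by-time ANOVA, and with two time points the interaction in that model is again a change-score comparison.

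Two things are at stake: power for the between-arm question, and an estimate that stays shifted by whatever baseline gap chance produces between two arms.

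**Working it through.** **The plan's own figure.** The inputs in Sample size {14} are "paired samples were considered, with α=5% and an 80% test power", and "The minimum number in this clinical trial was determined to be 34 teeth per group". The effect size and SD are not in the text (the figures that may hold them are not shown), so 34 cannot be reproduced from stated inputs. A two-sided paired t-test returns 34 if the standardised effect is 0.5 (range 0.495 to 0.503). Allowing for 15% loss, 34 / 0.85 = 40. That calculation sizes a before/after test within teeth. It does not set the power of an arm comparison, which is worked out here.

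**Inputs for the arm comparison.** n = 34 per arm (Sample size {14}); α = 5% (Statistical methods {20a}), taken as two-sided. Assumed: normal log10 counts with equal SD before and after, and a true difference of 0.69 SD, chosen because it gives an unadjusted two-arm t-test 80% power at 34 per arm. The correlation r between the two counts is not in the documents, so a range is shown.

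**Formulas.** In units of the post-treatment SD, the residual SD is
- post-treatment count only: 1
- change from baseline: √(2(1 − r))
- ANCOVA: √(1 − r²)

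Noncentrality = 0.69 × √(34/2) / residual SD = 2.845 / residual SD. Power then comes from the noncentral t with 66 degrees of freedom (65 for ANCOVA). Simulated values are in brackets.

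| r | Mann-Whitney, post count (simulated only) | Change score | ANCOVA |
|---|---|---|---|
| 0.2 | 77% | 60% (61%) | 82% (81%) |
| 0.3 | 78% | 66% (65%) | 84% (83%) |
| 0.5 | 78% | 80% (80%) | 90% (90%) |
| 0.7 | 76% | 95% (95%) | 97% (97%) |

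The Mann-Whitney figure does not depend on r; its spread is simulation noise. About 2 points of its gap to ANCOVA come from using ranks on normal data (78% against 80% for the t-test), and the rest comes from adjustment. Residual variance under ANCOVA relative to post-only is 1 − r² = 0.91, 0.75 and 0.51 at r = 0.3, 0.5 and 0.7.

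**Why neither planned option wins.** 2(1 − r) − (1 − r²) = (1 − r)², which is positive for r below 1, so the change score is always noisier than ANCOVA. 1 − r² is below 1 for any r above 0, so post-only is too. The change score is worse than post-only when 2(1 − r) > 1, that is, below r = 0.5.

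**A smaller effect.** At an assumed 0.5 SD and 34 per arm (normal approximation), power is 54% post-only against 56%, 58%, 66% and 82% adjusted at r = 0.2, 0.3, 0.5 and 0.7. Simulated on ranks, it is about 50% for Mann-Whitney against 51%, 53%, 61% and 76% for rank ANCOVA.

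**Validity.** With no true difference, simulated rejection stayed near 5% for every method.

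**Chance imbalance.** The SD of a baseline difference between two arms is √(2/34) = 0.243 SD. A gap above 0.25 SD has a 30% chance for a given pair of arms. At the two-sided 5% limit the gap is 1.96 × 0.243 = 0.475 SD. It moves a post-only estimate by r × 0.475 = 0.14, 0.24 or 0.33 SD at r = 0.3, 0.5 or 0.7, and a change-score estimate by (1 − r) × 0.475 = 0.33, 0.24 or 0.14 SD in the opposite direction. ANCOVA removes the shift.

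**Is the baseline clean?** In Intervention description {11a}, Group 1 lists prophylaxis between the initial radiograph and the first sample. Groups 2, 3 and 4 list no prophylaxis. Sequence generation {16a} has the envelope drawn at the time of treatment. The first sample may therefore differ by arm for Group 1. Among Groups 2 to 4 the steps listed before it are the same.

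**The case against.** **What a reader might infer, and why the document does not support it.**

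- *That the arm comparison ignores the baseline.* The text does not say so. It leaves the analysed variable open, and the objectives speak of counts before and after treatment, which would fit a test on change. An article may leave that definition to an analysis plan. What the article does fix is a set of tests with no baseline adjustment, and both available readings lose to ANCOVA.
- *That chance imbalance makes the planned tests invalid.* It does not; overall type I error is near 5%. False-positive rates above 5% arise only when one conditions on a particular gap having occurred.
- *That the wide entry range, from ICDAS 3 to* "or 5 (distinct cavity with visible dentine) of the International Caries Detection and Assessment System criteria (ICDAS"*, makes adjustment especially valuable.* The gain depends on r, not on baseline spread as such, and the exclusion criteria narrow the lesions admitted.
- *That CFU data are bound for the rank tests.* Simulated raw lognormal counts (log10 SD 0.5 to 1.0, n = 34) fail Shapiro-Wilk in at least 99.9% of samples, but the protocol does not say that raw counts are what is tested. The point holds in either branch.

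**What stands against the point.** The correlation may be low, because tissue is removed and in some arms an antimicrobial agent is applied between the two samples. At r = 0.2 to 0.3, adjustment itself is worth only about 2 to 5 points of power. The calculations assume no detection floor; many non-detects after treatment would reduce the gain. Most seriously, if prophylaxis changes the Group 1 first sample, ANCOVA carries the regression slope times that change into every contrast with control, whereas a post-only comparison does not. This limits where the adjusted analysis can be used without further work.

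**Conclusion.** The point holds as one of efficiency. The protocol names between-arm tests for a primary, sized outcome that do not adjust for a baseline already measured on every tooth, and it leaves the compared quantity open. At 34 per arm and an assumed 0.69 SD, power is about 78% for Mann-Whitney on post-treatment counts against 83%, 90% and 97% for ANCOVA at r = 0.3, 0.5 and 0.7. If change scores are used instead, power is 65%, 80% and 95%. The ordering does not rest on the assumed effect; the size rests on r, on roughly normal log counts and on few non-detects. The conclusion is clear for contrasts among Groups 2 to 4, and conditional for contrasts with Group 1 until the steps before the first sample are reconciled.

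**What to change.** In Statistical methods {20a}, replace the Shapiro-Wilk-driven choice for CFU counts with one prespecified analysis, settled before outcome data are compared by arm:

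1. Primary: ANCOVA of log10 post-treatment CFU on arm and log10 pre-treatment CFU. Back-transform the arm differences to ratios with 95% confidence intervals.
2. State a fixed rule for non-detects before taking logs.
3. Sensitivity: rank ANCOVA on the same two counts, which tolerates non-detects better.
4. Apply this directly to contrasts among Groups 2, 3 and 4.
5. For contrasts with Group 1, reconcile the group lists in Intervention description {11a} so that the first sample is taken under the same conditions in all arms. Where that was not so, report the unadjusted post-treatment comparison with Group 1 alongside the adjusted one.

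Items 1 to 4 cost one degree of freedom and a little more analysis work; they need no new samples, visits or participants. Item 5 is more than a wording change to the analysis, because it concerns procedure and cannot be put right for teeth already sampled. That is why the two comparisons are reported side by side.
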